### Follow-up

For each participant, the study will start at randomization, and the patient will be followed until 12 months after surgery. The primary outcome parameter will be evaluated every 3 months after surgery. During the 1 year of follow-up, data on readmission, functional results, and quality of life will be generated. Study visits will be scheduled to take place 4 weeks before surgery and 1, 3, 6, 9, and 12 months after surgery. The functional outcomes are the pyloric transit, bile reflux, oral intake, and gastrointestinal symptom questionnaires.

### Statistical methods

The Mann–Whitney *U*-test will be used to compare continuous variables such as weight change, which is the primary endpoint; body composition; and blood test indices. Student’s *t*-test (two-tailed) will be used to compare the mean parameters, and the chi-square test will be used to compare the bivariate variables such as the presence of perioperative complications.

Further subgroup analysis will only be carried out in case of significant interaction effects. The Wilcoxon signed rank test will be used to determine significant effects. Comparisons between the mH-P and control group for weight change either pre- or postoperative 6 months will be performed. Differences with a *p* < 0.050 are considered statistically significant.

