**Assessments**								
**Baseline patient characteristics**	X							
**Baseline tumor characteristics**	X							
**Body composition**	X		X	X	X	X	X	X
**Laboratory data**	X		X	X	X	X	X	X
**Postoperative outcome data**		X	X					
**Pathological data**			X					
**Oncological follow-up data**				X	X	X	X	X
**Gastroendoscopy**						X		X
**Computed tomography**				X	X	X	X	X
**QOL questionnaires**			X	X	X	X	X	X

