### Outcomes

The primary endpoint is the rate of body weight loss at 6 months after surgery. The secondary endpoints are oral intake and change in nutritional status, which will be checked during the perioperative hospitalization period and at 1, 3, 6, 9, and 12 months after surgery.

Oral intake will be calculated as a percentage of total energy expenditure, which will be calculated based on the weight and activity coefficient of each patient, and data will be collected at each time point. As the nutritional status of the patient will be monitored by body composition which is analyzed by a bioimpedance analyzer (InBody S10®). The analyzer determines the total body fat mass (kg) and skeletal muscle index (kg/m^2^). Additionally, blood tests will be performed at fixed points to measure nutritional evaluation indices (albumin, pre-albumin, cholesterol, total protein, lymphocyte count, and C-reactive protein).

Intraoperative factors such as the total blood loss, operation time, thoracic approach, subtotal gastric remnant or gastric tube reconstruction, and inclusion or exclusion of Kocher mobilization will also be analyzed.

To evaluate the degree of pyloric transit as a secondary endpoint, the amount and nature of decompressed gastric drainage and the pH and bilirubin level of the drainage will be measured on postoperative days 1, 3, 5, and 7. On day 7, the degree of pyloric drainage and the presence or absence of reflux will be assessed by oral contrast according to the standard clinical path. The blood and gastric drainage measurements will be taken in the laboratory, the data will be recorded in the medical record, and the sample will be discarded. The decompression tube will be clamped at 6:00 am to equalize the condition of the reconstructed elevated stomach, and contrast examination will be performed at 9:00 am on the same day. The contrast medium will be barium diluted to 60%.

The pyloric transit (an objective index) as evaluated by oral barium contrast will be scored according to the presence or absence of gastric contents in the reconstructed elevated stomach at the beginning of the examination (0: no, 1: yes), the pyloric transit time of the contrast medium (0: < 1 s, 1: > 1 s), and stagnation of the contrast medium in the stomach (0: completely disappears; 1: more than half remains; 2: all remains).

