	Exclusion criteria (1) Swallowing problems and poor oral intake associated with swallowing dysfunction (2) Weight loss of ≥ 20% within 6 months before surgery (3) Any synchronous active advanced cancer or diseases that affect the nutritional status (4) Medical history of DGE (5) Simultaneous resection for gastric cancer, other pyloroplasty procedures (e.g., finger bougie technique, Heineke–Mikulicz strictureplasty, or botulinum toxin injection), or Roux-en-Y reconstruction during the trial (6) Clinical condition inappropriate for participation in this study as judged by patient’s physician
Study type	Interventional
	Open randomized, single-center superiority trial. Patients will be randomly allocated to undergo gastric remnant reconstruction with modified Horsley pyloroplasty or no intervention in parallel groups
	Primary purpose; prevention
	Phase III
Date of first enrollment	2 September 2021
Target sample size	140; 70 vs 70
Recruitment status	Recruiting
Primary outcomes	Body weight change at 6 months postoperatively
Key secondary outcomes	Nutritional status, postoperative complications, functional outcome, and quality of life until 1 year postoperatively

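### Body composition and blood nutritional indices are compared by an unadjusted Mann–Whitney test although preoperative values are collected; adjusting for them is a cheap gain in efficiency, of a size that depends on an unstated correlation

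*Protocol article*

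**What the plan says.** The Statistical methods section of the protocol article fixes the between-arm test: "The Mann–Whitney *U*-test will be used to compare continuous variables such as weight change, which is the primary endpoint; body composition; and blood test indices". The other test that it names for continuous data is Student's t-test, "two-tailed) will be used to compare the mean parameters", which is also unadjusted. No model with a covariate appears anywhere in the article.

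The schedule in Table 1 marks the rows "Body composition" and "Laboratory data" at enrollment, at 2 weeks, and at 1, 3, 6, 9 and 12 months. Each patient should therefore have a preoperative value of these measures.

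The Outcomes section says: "The secondary endpoints are oral intake and change in nutritional status". It then lists total body fat mass, skeletal muscle index and the blood indices (albumin, pre-albumin, cholesterol, total protein, lymphocyte count and C-reactive protein).

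Table 3 gives the key secondary outcomes as "Nutritional status, postoperative complications, functional outcome, and quality of life until 1 year postoperatively", with nutritional status first.

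**The concern.** Two things stand out.

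- **The quantity tested is not fixed.** The sentence naming the test speaks of change only for weight. For body composition and blood indices it names classes of variable. The Outcomes section speaks of change in nutritional status, so change is the more natural reading, but the Statistical methods section does not settle it.
- **Under either reading the baseline is not used as a covariate.** A comparison of follow-up values ignores it. A comparison of changes uses it by subtraction, which is efficient only when baseline and follow-up are very highly correlated. A model with the baseline as covariate lets the data set the weight.

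What is at stake is precision on the first-listed key secondary outcome, in a single-center trial of 140 patients whose Discussion ties possible wider adoption of the procedure to nutritional status. A real effect on muscle index or pre-albumin could be missed although the collected data could have shown it.

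**Working it through.** The plan states no effect size, SD, correlation or power for these endpoints, so there is no figure of its own to reproduce. The Sample size section covers the primary endpoint only.

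**Inputs**
- From the protocol: 60 evaluable patients per arm and a two-sided test at 0.05 (Sample size; Statistical methods).
- Assumed: correlation rho between preoperative and follow-up value, 0.3 to 0.9; equal SD (set to 1) at both times; normal data; 80% power for the unadjusted analysis as a reference point.
- Assumed: the laboratory row of Table 1 includes the nutritional blood indices.

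**Step 1: variance of each analysis (per patient)**
- Follow-up value, unadjusted: 1
- Change, unadjusted: 2(1 − rho)
- ANCOVA with baseline as covariate: 1 − rho²

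The ratio R of ANCOVA variance to unadjusted variance is 1 − rho² against follow-up values. Against change it is (1 − rho²) / [2(1 − rho)] = (1 + rho)/2. Neither exceeds 1. At rho = 0.5 both are 0.75, a 25% cut.

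**Step 2: power**

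80% power means effect/SE = 1.960 + 0.842 = 2.802. Adjustment multiplies the SE by √R, so adjusted power = Φ(2.802/√R − 1.960).
- rho 0.5, either reading: 2.802/√0.75 = 3.235; Φ(1.275) = 0.899.
- rho 0.9, change: 2.802/√0.95 = 2.874; Φ(0.914) = 0.820.
- rho 0.7, follow-up values: 2.802/√0.51 = 3.923; Φ(1.963) = 0.975.

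| rho | Adjusted power if change has 80% | Patients needed, change vs ANCOVA: 2/(1 + rho) | Adjusted power if values have 80% | Patients needed, values vs ANCOVA: 1/(1 − rho²) |
|---|---|---|---|---|
| 0.3 | 94% | 1.54 | 84% | 1.10 |
| 0.5 | 90% | 1.33 | 90% | 1.33 |
| 0.7 | 86% | 1.18 | 98% | 1.96 |
| 0.8 | 84% | 1.11 | over 99% | 2.78 |
| 0.9 | 82% | 1.05 | over 99% | 5.26 |

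The number per arm cancels once the starting power is fixed, so the power columns do not depend on 60 being exact.

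**Step 3: check with the actual rank test**

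Simulation at rho 0.5, 60 per arm, effect 0.515 SD, 4,000 runs: Mann–Whitney on values 79%, Mann–Whitney on change 78%, ANCOVA 90%. With no effect, ANCOVA rejected in 4.95% of runs.

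A second simulation (8,000 runs per rho, normal data) set the effect so that ANCOVA has about 80% power:

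| rho | Mann–Whitney, values | Mann–Whitney, change | ANCOVA | Rank-based ANCOVA |
|---|---|---|---|---|
| 0.3 | 74% | 59% | 79% | 77% |
| 0.5 | 65% | 64% | 79% | 76% |
| 0.7 | 49% | 70% | 79% | 75% |
| 0.8 | 37% | 72% | 79% | 74% |
| 0.9 | 21% | 75% | 79% | 72% |

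These gaps include the rank test's own small cost under normality (relative efficiency 3/π = 0.955). Linear ANCOVA is ahead throughout. Rank-based ANCOVA is ahead of Mann–Whitney on change up to rho 0.8 but slightly behind at 0.9.

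**Step 4: the ambiguity disappears under adjustment.** If value = a + b·arm + c·baseline, then value − baseline = a + b·arm + (c − 1)·baseline. The arm effect b is the same, so it no longer matters whether the outcome is the value or the change.

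**The case against.** The case on the other side is strong on several points.

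- **No error is shown.** A two-group rank test is valid under randomization and its error rate already allows for chance imbalance. No power is claimed for these endpoints, so no stated figure fails. This stands, and it limits the point to efficiency.
- **A substantial loss of power is not established.** A reader might infer one as a fact. The documents do not support that: it depends on a correlation that they do not give and on which quantity is tested. Under the change reading, the formula gain is only 4 points at rho 0.8 and 2 points at rho 0.9. This stands.
- **The large figures belong to the less supported reading.** A reader might also infer that raw values are tested and the baseline goes unused. The Outcomes section points to change, which uses the baseline by subtraction. Nor do all indices carry differences in body size: skeletal muscle index is already scaled (kg/m²), and most of the blood indices are concentrations. This stands too.
- **These are supportive outcomes.** The Objectives section gives the main nutritional role to body weight. That is fair, but Table 3 still lists nutritional status first among the key secondary outcomes.
- **Normal data favour linear ANCOVA, and C-reactive protein is skewed.** No gain has been shown here for skewed indices. This is a reason to transform or to use ranks for them, not a reason to leave the baseline out for all.
- **Covariates for secondary endpoints are usually left to the analysis plan.** Silence would be no finding. Here, however, the article names a test for these variables, and that choice can be judged.

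**Conclusion.** The point holds as a free or cheap improvement, not as an error or a source of bias. The stated test is valid, leaves the analysed quantity open for body composition and blood indices, and makes less use of the collected preoperative values than baseline adjustment would.

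Under the more natural change reading, the gain from a starting power of 80% is between 2 points (rho 0.9) and 14 points (rho 0.3). Under the raw-value reading it runs from 4 points (rho 0.3) to nearly 20 (rho 0.8 or more). These sizes rest on an assumed rho, equal SDs before and after surgery, and normal data; none of these is given in the protocol.

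**What to change.** In the Statistical methods section, for fat mass, skeletal muscle index and each blood nutritional index:

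- Analyse the postoperative value by ANCOVA at each visit, or by one repeated-measures model over 1, 3, 6, 9 and 12 months, with the patient's own preoperative value of the same measure as covariate.
- Report the adjusted difference between arms with its 95% CI.
- For skewed indices such as C-reactive protein, use a log transform or rank-based ANCOVA. The log transform is the better first choice where rho may be near 0.9, given the simulation above.
- Keep the Mann–Whitney comparison as a sensitivity analysis, and state whether it is made on values or on changes.

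The cost is a change of analysis wording, best dated before any unblinded comparison of these endpoints. No new visit or measurement is needed. The small downside is a model assumption, which the transform and the retained rank test cover.

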### Sample size

The primary endpoint of this trial is the determination of the rate of change in the postoperative body weight. The sample size required to predict the number of patients necessary for statistical validity (two-sided test) is based on our retrospective data from June 2019 to June 2020 (*n* = 20). These are unpublished data. According to these data, the average rate of body weight loss at 6 months postoperatively is − 4.2% in the mH-P group and − 8.2% in the NI group. The incidence rate of the average body weight loss in the mH-P group is expected to be ≤ 4%. We calculated that 60 patients will be required in each arm of this study with a significance (*α* level) of 0.05 and power (1 − *β*) of 0.8. Anticipating a 5% rate of loss to follow-up, we calculated that 70 patients will be required in each arm of this study (total study population of 140 patients).

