### Interim analyses

Two interim analyses will be performed during the course of the study to determine whether the primary objective of the study has been achieved. The first interim analysis will be performed during enrollment to determine whether it is appropriate to continue enrollment, and the second interim analysis will be performed early after the end of enrollment to determine whether to continue follow-up for the planned period. In either case, if it is determined that the primary objective of the study has been achieved, the study will be terminated, and the results will be promptly published in conferences and papers.

The first interim analysis will be conducted using data from periodic monitoring when half of the expected number of enrolled patients have completed 1 year of follow-up. The second interim analysis will be conducted in conjunction with periodic monitoring at a time deemed appropriate after consultation between the data center and the CRC, around the time when enrollment is completed, and protocol treatment is completed for all enrolled patients. In principle, enrollment will not be stopped during the first interim analysis. The decision criteria based on the results of the interim analysis of this study will be as follows. If the non-inferiority of the mH-P group to the NI group for the primary endpoint is not demonstrated, or if non-inferiority is demonstrated but superiority is not demonstrated, the study will be continued in either case. If non-inferiority of the primary endpoint of mH-P over NI is demonstrated and superiority is also demonstrated, the study will be terminated (effective termination). If the primary endpoint of the mH-P group is lower than that of the NI group, the need for discontinuation of the study will be comprehensively considered without being restricted by statistical judgment such as tests (invalid discontinuation).

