### Oversight and monitoring

An independent data and safety monitoring committee will evaluate the progress of the trial and examine safety variables. The committee will consist of a surgeon, CRCs, and a statistician. Individualized patient description charts including safety parameters will be presented to the committee, including one table comprising these endpoints in blinded groups every 6 months. The main safety parameters are all serious adverse events (AE): mortality, multiple organ failure, anastomotic leakage, pulmonary complications, cardiovascular complications, reinterventions, and reoperation. After the investigators have presented the data, the members of the committee will discuss these results in the absence of the investigators and will then advise them. Possible options will include continuing the trial, performing an interim analysis, adjusting the trial’s design, and discontinuing the trial. Discontinuation will be advised if the committee concludes that the results would convince a broad range of clinicians that one trial arm is inferior or if safety is compromised in one arm. If the committee advises adjustment of the trial’s design, performance of an interim analysis, or discontinuation of the trial, the responsible medical ethical committee will also be notified. Serious adverse events (SAE) will be reported to the chairman of the hospital. The PYNI-GAREREO trial will be monitored according to the Japanese ethical guidelines for medical and health research involving human subjects. This is a low-risk study because both interventions being investigated are considered to be standard care in Japan.

In-house monitoring will be performed every year by a third party to evaluate and improve the progress and quality of the study. A Patient and Public Involvement (PPI) member will not be part of the committee.

The first interim analysis will be conducted after half of the planned number of patients are enrolled, and the second interim analysis will be conducted immediately before the planned patient accrual is completed. The data and safety monitoring committee will review the interim analysis reports independently from the investigators and statistician. In-house monitoring will be performed every 6 months by a data center to evaluate and improve the study progress, data integrity, and patient safety.

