## Trial status

The trial has been recruiting since September 2021. This trial recruitment will end when the planned number of patients have been enrolled or depending on the results of the interim analyses. We plan to conduct two interim analyses. The first interim analysis will be conducted after half of the planned number of patients have been enrolled, and the second interim analysis will be performed immediately before the planned patient accrual has been completed. The data and safety monitoring center will review the interim analysis reports independently from the group investigators and group statistician. If the superiority of the mH-P group is demonstrated with an adjusted α level, the study will be terminated. In-house monitoring will be performed every 6 months by the data center to evaluate and improve the study progress, data integrity, and patient safety.

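### The primary endpoint is declared significant at p < 0.050 although two interim looks may already have spent alpha; no final level is set to keep the overall error at 0.05

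*Protocol article*

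**What the plan says.** All places are in the protocol article.

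- **Sample size:** two-sided test, alpha 0.05, power 0.8, 60 patients per arm before allowance for loss to follow-up. No allowance for interim looks is mentioned.
- **Statistical methods:** weight change is named as the primary endpoint, and differences with p "< 0.050 are considered statistically significant". This is the only numerical significance threshold in the article.
- **Interim analyses:** the section opens with their number and purpose: "Two interim analyses will be performed during the course of the study to determine whether the primary objective of the study has been achieved". If superiority of pyloroplasty is shown at a look, the trial ends and is published. The decision criteria here carry no significance level.
- **Trial status:** "If the superiority of the mH-P group is demonstrated with an adjusted α level, the study will be terminated". No value, method or final level follows.
- **Oversight and monitoring:** the committee may advise further steps: "Possible options will include continuing the trial, performing an interim analysis" is how the list begins. No endpoint or level is attached.
- **Timing of the looks:** under Interim analyses, the first look comes when half the patients have a year of follow-up, and the second around or soon after the end of enrolment. Under Oversight and monitoring and under Trial status, the first comes once half are enrolled, and the second just before accrual closes.

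**The concern.** The primary hypothesis can be declared proven at three points: two interim looks and the final analysis. Any chance of a false positive at the interim looks adds to the chance at the end. To hold the total at 0.05, the final test must use whatever is left after the interim looks, which is always less than 0.050. The article adjusts the interim stop but leaves the final rule at the full 0.050.

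At stake is whether the stated two-sided 5% is true for a trial that, according to its Discussion, could make this pyloroplasty a standard additional procedure. The final threshold also has to be settled before the first look to be credible.

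**Working it through.** **Inputs from the article.** Two-sided alpha 0.05 and power 0.8 (Sample size); threshold 0.050 (Statistical methods); two efficacy looks (Interim analyses); adjusted, but unspecified, interim level (Trial status).

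**Assumed inputs.** The article gives no accrual rate and describes the look timings in two ways, so the information fractions t are assumptions: 0.5, then 0.9 or 0.95, then 1. Earlier looks serve as a sensitivity check. The interim levels are also assumed, one scheme at a time. The statistics are treated as approximately normal, which is reasonable for a rank test or a t-test at this size. The standard deviation, which the article does not give, is not needed for the type I error.

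**Formula.** With two-sided critical values c1, c2, c3 and corr(Zi, Zj) = √(ti/tj) for ti < tj,

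overall error = 1 − P(|Z1| < c1, |Z2| < c2, |Z3| < c3).

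**Step 1: the plan's own figure.** One final test at 1.960 gives 0.050. The stated 0.05 is correct only if the interim looks spend nothing.

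**Step 2: interim levels.** For O'Brien-Fleming-type spending of the total 0.05, cumulative alpha at t is 2[1 − Φ(1.960/√t)]. At t = 0.5 this is 2[1 − Φ(2.772)] = 0.0056; at t = 0.9 it is 2[1 − Φ(2.066)] = 0.0388. Solving for the critical values gives nominal levels of 0.0056, 0.0367 and 0.0368. Spending 0.025 on each side instead gives 0.0031, 0.0353 and 0.0397.

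**Step 3: keep these interim levels, but run the final test at 0.050.** The last column is the final level that would hold the total at 0.05.

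| Interim scheme | Error, looks 0.5/0.9/1 | Error, looks 0.5/0.95/1 | Correct final level, 0.5/0.9/1 |
|---|---|---|---|
| Haybittle-Peto, 0.001 at each interim | 0.0502 | 0.0502 | 0.0498 |
| O'Brien-Fleming-type spending, 0.025 per side | 0.0576 | 0.0571 | 0.0397 |
| O'Brien-Fleming-type spending, 0.05 in total | 0.0592 | 0.0582 | 0.0368 |
| Pocock (equal level at each look) | 0.0670 | 0.0664 | 0.0256 |

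**Step 4: sensitivity to earlier looks.** At 0.33/0.67/1 and 0.25/0.75/1, with the final test at 0.050, Haybittle-Peto gives 0.0505 and 0.0506, classical O'Brien-Fleming boundaries 0.0546 and 0.0555, and Pocock levels 0.072 in both. Every case exceeds 0.05.

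**Step 5: direction.** These totals count interim crossings in either direction. By symmetry, a false claim in favour of pyloroplasty has half the total: with O'Brien-Fleming-type spending at 0.5/0.9/1, 0.0576/2 = 0.029 to 0.0592/2 = 0.030, against a nominal 0.025. If the interim looks can succeed only in favour of pyloroplasty, the total is about 0.029 + 0.025 = 0.054 to 0.030 + 0.025 = 0.055.

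**Step 6: power after correction.** Let the final statistic have mean 1.960 + 0.842 = 2.802 (80% power at a single test at 0.05) and the interim statistics mean 2.802√t. At 0.5/0.9/1 with correct final levels, power is about 0.80 with Haybittle-Peto, 0.786 to 0.790 with O'Brien-Fleming-type spending, and 0.756 with Pocock.

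**The case against.** The strongest reply is that the article already plans a sequential adjustment. The Trial status section says so, a condensed article commonly leaves the method and nominal levels to the full protocol or analysis plan, and the 0.050 sentence closes a paragraph that also covers other endpoints and never says final. An overall alpha of 0.05 in the sample size does not by itself show that the last test uses 0.05.

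Much of this stands. The missing method is not itself the finding, and if the adjustment also lowers the final level there is no excess. What remains is that the article states a threshold in the section that names the primary endpoint, and that threshold cannot be right once any alpha is spent. An analysis plan with a lower final level would contradict that sentence, which would still need correcting.

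Two stronger readings are tempting, and the article supports neither.

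- A reader might infer that all three analyses are run at 0.05. The error would then be 0.091 to 0.094 at the fractions in the table, 0.097 with looks at 0.5/0.75/1, and up to 0.109 with earlier looks (about 0.072 to 0.073 if interim looks can succeed only in favour of pyloroplasty). The Trial status section rules this out by requiring an adjusted level for an interim stop.
- A reader might count the committee's six-monthly reviews as extra efficacy tests. They are reviews of progress and safety in blinded groups. An interim analysis is only one thing the committee may advise, with no efficacy test described. It is an open route to an uncontrolled look, not a planned source of error.

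**Conclusion.** The point holds in a limited form. The p < 0.050 rule for the primary endpoint is not reconciled with two looks that can end the trial for superiority. Followed as written, it gives an overall two-sided error above the stated 0.05: by about 0.0002 with very strict interim levels, by 0.007 to 0.009 with O'Brien-Fleming-type spending, and by 0.016 to 0.017 with Pocock levels.

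These figures rest on assumed information fractions, on an assumed interim scheme, on counting crossings in both directions, and on the final test being run at 0.050. If only interim crossings in favour of pyloroplasty count, the excess is about half. If an unseen document lowers the final level, it is zero and only the wording is wrong. An error of 0.09 to 0.10 should not be attributed to this plan.

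**What to change.** Before the first interim look:

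1. State that 0.05 two-sided is the overall level for the primary endpoint across both interim looks and the final test.
2. Name the adjustment method in the Interim analyses section. The choice belongs to the sponsor.
3. In the Statistical methods section, replace p < 0.050 for the primary endpoint with the level left after the interim looks. At 50/90/100% of the information, examples are about 0.037 to 0.040 with O'Brien-Fleming-type spending (depending on whether 0.05 is spent in total or 0.025 per side), or about 0.0498 with Haybittle-Peto at 0.001. The 0.050 threshold can stay for the other endpoints.
4. Reconcile the timing of both looks between the Interim analyses section and the Oversight and monitoring and Trial status sections, so that the levels can be derived.
5. State that any efficacy look advised by the committee falls under the same method.

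The cost is a paragraph of text and a somewhat stricter final threshold. At an unchanged sample size, power falls from 0.80 by about 1.0 to 1.4 percentage points with O'Brien-Fleming-type spending (0.790 to 0.786), by a negligible amount with Haybittle-Peto, and by more than 4 points with Pocock levels.
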